### Recruitment measures

Four sites with extensive experience and expertise in the investigation and treatment of children and adolescents with ASD participate in the trial: (1) the Department of Child and Adolescent Psychiatry, Psychosomatics and Psychotherapy and Autism Research and Intervention Center of Excellence at the University Hospital Frankfurt, Goethe University; (2) the Department of Child and Adolescent Psychiatry, Psychosomatics and Psychotherapy at Bethel Protestant Hospital in Bielefeld, Germany (3) the ICNAS, Centro Clínico Académico, Universidade de Coimbra, Portugal; and (4) the Centre Hospitalier Regional Universitaire de Tours, Tours, France. All sites are associated with large in- and outpatient departments, so families and adolescents with ASD can be approached and specifically invited to participate in the study. Additional patients will be approached via flyers and by announcements published in the local newspapers and on the internet. Local paediatricians, child and adolescent psychiatrists and psychotherapists as well as ASD patient and parent organizations will be informed about the study.

### Assignment to study arm / randomization

After definite inclusion into the study (signed informed consent, fulfilment of all inclusion criteria), each patient will be allocated randomly to one of the two treatment conditions (anodal tDCS stimulation or sham stimulation) via the electronic case report form (eCRF) using a stratified block randomization. Randomization will be stratified by site and gender. Block randomization for each stratum is prepared with the electronic randomization tool BiAS for Windows. Randomization is performed by Institute of Medical Informatics and Statistics (IMIS)/Center for Clinical Trials (ZKS) Kiel.

### Blinding

Subjects, parents and study personnel will be blinded to treatment allocation for the whole duration of the trial. The device Starstim32 (Neuroelectrics SLU, Barcelona, Spain) allows to perform double-blind stimulation. Prior to study start, an administrator at Neuroelectrics who can create and manage stimulation protocols creates templates for real and sham stimulation. Each centre receives a series of files from the statistician which do not reveal any information of the condition (tDCS or sham). At randomization, one specific file is assigned to each participant via the eCRF. During the stimulation session, the study personnel will have no access to the password-protected content of this file (protocol data, i.e. currents, sham-settings) and thus remain effectively blinded.

Unblinding will be done in case of the following emergencies: unblinding is necessary for reasons of subjects’ safety and for decisions on further medical treatment and a serious adverse device effect (SADE) has to be unblinded for notification to authorities and ethics committees. Unblinding will be performed through emergency envelopes on site, which contain information on sham or real stimulation. The participant and his/her parents must be informed about unblinding. Unblinding leads to the exclusion of the respective participant from further intervention sessions.

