### Statistical methods

The planned sample size was calculated using a two-sided *t*-test (significance level *α* = 0.05) with a power 1−*β* = 80% based on a medium expected effect size of *d* = 0.6. Previous studies in ASD have shown similar or larger effect sizes for tDCS [71]. This effect requires a sample size of 45 patients per group (G*Power 3.1); assuming 10% drop-out, the total sample size will thus consist of 100 individuals randomized to tDCS or sham.

The primary analysis will be based on the intention-to-treat (ITT) set, including all randomized patients irrespective of the amount of treatment actually received or adherence to the intervention. A per-protocol (PP) analysis will be performed as sensitivity analysis with only those participants who received at least 9 out of 10 stimulation sessions without further relevant protocol deviations. In order to follow the intention-to-treat principle as closely as possible, all participants will be asked to participate in the end-of-treatment and follow-up assessment, even if they drop out of treatment, to minimize the amount of missing data.

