### Documentation and evaluation of adverse events

Previous studies in children have rarely reported serious adverse events (SAEs) and tDCS-related side effects generally seem to be mostly mild and transient (such as, e.g. tingling, itching, redness and scalp discomfort [27]). In the current trial, investigators record all adverse events (AEs) in an Adverse Event Log provided in the eCRF including time of onset and intensity, causal relationship, action taken and outcome. SAEs are documented in a Serious Adverse Event Log and additionally must be reported to the sponsor immediately. The sponsor will perform all SAE-reporting to responsible authorities according to applicable national laws. A SOP on handling SAEs is provided for all trial sites by the sponsor. In Germany, quarterly safety reports listing all SAEs will be provided by the sponsor. In France and in Portugal, annual safety reports will be submitted.

A DSMB with three independent members is installed, who will monitor safety data in fixed time intervals. The first meeting will be held after the tenth patient has been included in the trial. When 50% of the participants have been recruited, the second meeting will take place. Additional meetings will be organized on demand, e.g. in case of emergency, an unscheduled meeting can be performed. If necessary, the DSMB has access to the unblinded data to judge whether the risk-benefit ratio changes throughout the study. If the board decides that the safety of participants is significantly endangered, they can recommend stopping the study.

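### A code-break needed only to report a serious adverse device effect uses the on-site emergency envelope, so site staff learn the arm and the parent rating the primary outcome may learn it too

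*Protocol article*

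**What the plan says.** All of the unblinding procedure is in the Blinding section of the protocol article. It opens with the general commitment: "Subjects, parents and study personnel will be blinded to treatment allocation for the whole duration of the trial". It then lists the situations in which the code may be broken. One is clinical, for reasons of the participant's "safety and for decisions on further medical treatment". The other is regulatory: "a serious adverse device effect (SADE) has to be unblinded for notification to authorities and ethics committees".

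A single procedure follows, with no distinction between the two:

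- Route: "Unblinding will be performed through emergency envelopes on site, which contain information on sham or real stimulation".
- Family: "The participant and his/her parents must be informed about unblinding".
- Treatment: the participant receives no further intervention sessions.

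Three other sections bear on this:

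- Documentation and evaluation of adverse events: "The sponsor will perform all SAE-reporting to responsible authorities according to applicable national laws".
- Outcome measures: the primary outcome, the SRS-16, is rated by the parent.
- Statistical methods: "all participants will be asked to participate in the end-of-treatment and follow-up assessment, even if they drop out of treatment". The primary analysis is by intention to treat and uses the SRS-16 from all time points, including T2-5 and T4.

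**The concern.** The two grounds have different needs. In a clinical emergency, someone at the site may have to know the arm. For a notification, only the person who completes the report has to know it, and here the report is the sponsor's responsibility. The article nevertheless sends both through an envelope opened at the site.

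Whoever opens the envelope learns the arm, so the blind of site staff is given up for an administrative purpose. The family must then be informed, and that family includes the rater of the primary outcome. If the arm is disclosed to them, any SRS-16 completed afterwards is an unblinded rating, and nothing in the article separates it from blinded ratings in the primary model. The participants concerned are those with a suspected serious device effect, in a trial that names safety as a second primary objective.

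This is a route that the article states, not a detail that it leaves out. It also sits oddly with arrangements already in place. Randomisation is performed at IMIS/ZKS Kiel and the coded stimulation files come from the statistician, so knowledge of the allocation already exists away from the sites.

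**Working it through.** **Reading the sections together**

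1. *Are there two grounds or one combined ground?* They are joined by 'and', but they follow an introduction that announces emergencies in the plural. Two separate situations is the more natural reading. If both had to apply at once, a reporting-only code-break could not occur. The text should say which is meant.
2. *Which route applies to the regulatory ground?* Only the on-site envelope is named.
3. *Who learns the arm?* Certainly the person who opens the envelope. The family is told about the unblinding; whether they are told the result is not stated.
4. *Do later ratings count?* Yes. Stopping sessions does not end assessment, and the primary set is all randomised participants. The T2 baseline precedes the first session and is unaffected. T2-5, T3 and T4 ratings may be affected, depending on when the code is broken.

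**The plan's own figure**

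The point rests on no stated figure, but the sample size gives the scale. For a two-sided two-sample t-test with alpha = 0.05, power 80% and d = 0.6, the noncentral t calculation gives n = 44.59, rounded up to 45 per group (power 80.4% at 45). Allowing for 10% drop-out, 90 / 0.9 = 100. Both figures in Statistical methods reproduce, and this point does not change them.

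**Size of the possible bias**

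The article gives neither a SADE rate nor the effect of unblinding on a parent rating, so both are assumed. If k parents in one arm of n learn the allocation and each T3 rating moves by s SD in the same direction, the difference between arms moves by

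bias = (k / n) × s.

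With n = 45:

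| k | s = 0.5 SD | s = 1.0 SD |
|---|---|---|
| 0 | 0 | 0 |
| 1 | 0.5/45 = 0.011 | 1.0/45 = 0.022 |
| 2 | 1.0/45 = 0.022 | 2.0/45 = 0.044 |
| 3 | 1.5/45 = 0.033 | 3.0/45 = 0.067 |

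Relative to d = 0.6, the largest entry is 0.067 / 0.6 = 11%, and the smallest non-zero entry is 0.011 / 0.6 = 2%. The direction is unknown. The table puts all code-breaks in one arm.

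**How likely is any code-break?**

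The chance of at least one among 100 participants is 1 − (1 − p)^100. For assumed SADE rates p of 0.5%, 1% and 2% this is 39%, 63% and 87%, with 0.5, 1 and 2 events expected. At the lowest of these rates, no event at all is the more likely outcome (61%).

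**The case against.** **Emergency exceptions to blinding are normal.** A reader might infer that the procedure contradicts the promise of blinding throughout the trial. It does not: the commitment is followed directly by its listed exceptions, which is ordinary drafting. What remains is that one exception is wider than its purpose requires.

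**Being informed about unblinding is not the same as being told the arm.** A reader might infer that parents will learn the allocation. The sentence is equally compatible with telling them only that the code was opened. This stands, so the parent's loss of blind is possible, not certain. The loss for whoever opens the envelope is certain.

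**The fuller documents may provide a sponsor-side route.** The article mentions a sponsor SOP on handling SAEs, and a separate route for notification could be set out there. That is possible, but the article states how unblinding is done and names only the site envelope. If another route exists, the article's text misdescribes it.

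**The per-protocol analysis already covers this.** It does so in part. Unblinding ends the sessions, and that analysis requires at least 9 of 10, so a child unblinded before completing the ninth session drops out of it. A code-break after that point is not caught by the session count. The analysis also removes other children for unrelated reasons, so it does not isolate the effect of disclosure.

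**Knock-on effects are speculative.** A reader might infer that one opened envelope exposes other children in the same site-by-gender block, or that the examiner scoring the imitation test becomes unblinded. Block size is not given, nothing shows that staff know the block structure, and nothing says that the examiner opens or sees the envelope. Neither inference is relied on here.

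**The events are rare.** The article says that serious events have rarely been reported in children. This stands, and it limits the weight of the point.

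**Conclusion.** The point holds as a weakness of procedure. On the natural reading of the Blinding section, a SADE code-break that serves only notification is made at the site, although reporting belongs to the sponsor. It unblinds site staff without a stated clinical need and may unblind the parent who rates the primary outcome. Ratings made afterwards remain in the primary analysis.

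The expected effect on the estimate is small: 0.011 to 0.067 SD under the assumptions of one to three code-breaks, all in one arm of 45, and a shift of 0.5 to 1.0 SD each; zero if no SADE occurs or if the family is not told the arm. A reader might infer that the main result is in danger. Against a planned d = 0.6 and with rare events, the documents do not support that. The case for acting is that the loss of blind is avoidable, falls on the participants with suspected device harm, and is cheap to prevent.

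**What to change.** 1. For a SADE unblinded only for notification, have a designated person outside the trial team at the existing randomisation and data centre (IMIS/ZKS Kiel) break the code and supply it for the report, so that site staff and family stay blinded. The section Further information on the trial states that the sponsor's representative is also the coordinating investigator. The text should therefore name who may receive the code, rather than say only that it goes to the sponsor.
2. Record in the eCRF, for every code-break, the date, the ground and each person to whom the arm was disclosed. The date can then be set against each SRS-16 rating.
3. Add a sensitivity analysis of the primary endpoint that omits SRS-16 ratings made after disclosure to the rater and keeps that participant's earlier ratings.
4. State whether the two grounds for unblinding are separate, and whether informing the family means telling them that the code was opened or which arm it showed.
5. Reconcile the sentences on blinding, informing the family and ending sessions for a reporting-only unblinding. Which clinical rule should apply is for the sponsor and investigators to decide; none is proposed here.

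Cost: a paragraph in the protocol and in the SAE procedure, a few eCRF fields and one extra model run. The small downside is that the data centre must keep one designated unblinded contact. Sample size and the primary model are unchanged.

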### Intervention

The intervention consists of 10 sessions of either tDCS- or sham stimulation during a socio-cognitive training. The real stimulation is anodal stimulation of the TPJ at 2 mA for a duration of 20 min (plus 30-s ramp-up and 30-s ramp-down) per session. The control intervention is a sham stimulation (at the beginning 30-s ramp-up followed by 30-s fade out after 5 s and 30 s fade in and then 30 s ramp-down at the end, but no effective stimulation for the remaining duration of the intervention), which also has a total duration of 21 min including ramp-up and ramp-down. This type of sham stimulation is routinely used as a comparison to actual tDCS stimulation. The short transient application of current at the beginning and at the end induces the sensory impression of being stimulated and serves to improve the blinding of participants, while no meaningful changes in neural excitability is induced. The medical device used for the intervention (Starstim 32®, Neuroelectrics) is a transcranial current stimulation and EEG monitoring device. An optimized multi-channel montage is used to target the TPJ bilaterally based on an area identified using DTI-based tractography [68]. The target area covers regions of the TPJ which were identified as functionally relevant for social cognitive abilities [31]. The optimization method used is the Stimweaver algorithm [69], which determines the electrode positions and currents that better approximate a target distribution of currents in a computational numerical head model (Colin head model, [70]). The optimized montage consists of two anode-electrodes, one over the left and right TPJ each, with several cathode-electrodes placed around each anode. The maximal injected current into the brain at any given time will be below 2.00 mA and maximum current at any electrode is 1.00 mA. The electrodes used in this study are 1 cm radius Ag/AgCl cylindrical electrodes with conductive gel underneath (NG PiStim electrodes).

Both, the tDCS and sham groups, will perform a cognitive training battery targeting theory of mind and perspective taking abilities during the intervention sessions. The training battery consists of short film clips, followed by questions probing the participant’s understanding of the character’s intentions, thoughts or feelings. Depending on whether the participant chooses a correct or incorrect answer to the question, the participant will either have to explain how they knew the correct answer, or receive an opportunity to repeat the scene and question if an incorrect answer was given. Before the film clip is repeated, they will receive a prompt about what to attend to in order to answer the question correctly. If they do not succeed on the second attempt, detailed feedback will be presented to ensure the participant understood which answer was correct and why. This detailed feedback involves highlighting the salient expressions, body language or choice of words a character expresses. Rule-based explanations for a character’s action will be given. Emotions or facial expressions will be explained in detail, and other examples will be given to allow the participant to generalize from the film scene to other social situations. An experimenter is present with the participant, helps understand the questions and feedback and can motivate and encourage the child throughout the training.

### Statistical methods

The planned sample size was calculated using a two-sided *t*-test (significance level *α* = 0.05) with a power 1−*β* = 80% based on a medium expected effect size of *d* = 0.6. Previous studies in ASD have shown similar or larger effect sizes for tDCS [71]. This effect requires a sample size of 45 patients per group (G*Power 3.1); assuming 10% drop-out, the total sample size will thus consist of 100 individuals randomized to tDCS or sham.

The primary analysis will be based on the intention-to-treat (ITT) set, including all randomized patients irrespective of the amount of treatment actually received or adherence to the intervention. A per-protocol (PP) analysis will be performed as sensitivity analysis with only those participants who received at least 9 out of 10 stimulation sessions without further relevant protocol deviations. In order to follow the intention-to-treat principle as closely as possible, all participants will be asked to participate in the end-of-treatment and follow-up assessment, even if they drop out of treatment, to minimize the amount of missing data.

We will test for a difference in the primary outcome measure, the change in SRS-16 item short form between post-treatment (T3) and baseline (T2), between the two study arms using a mixed-effects model repeated measures analysis with covariates centre, gender, age, IQ and the baseline value of the primary outcome (SRS-16 at T2). No unadjusted analyses are planned. Emphasis will be on the 95% confidence intervals of the effect size estimates; additionally, *p* values will be calculated. Secondary outcomes and the additional outcomes at the follow-up assessment (T4) will be analysed in a similar way. No subgroup analyses are planned, and any post hoc subgroup analyses would be considered exploratory. In this clinical trial, any missing values of the primary outcome variable have to be considered to be missing not at random (MNAR), in particular patients with very poor response to the intervention might be more likely to drop out of treatment and might be more likely not to provide data on the primary outcome (loss to follow-up). Thus, imputation strategies or analysis methods that rely on the missing at random (MAR) assumption could be anti-conservative. In the primary analysis of the primary endpoint, we will use all available measures of the primary outcome (SRS-16) at all time-points (in particular T2-5 and follow-up T4) in a mixed-effects model repeated measures analysis without imputation of missing values. Sensitivity analyses will be performed to investigate the potential impact of missing data, in particular, by performing a complete case analysis and a pre-specified conservative single imputation approach and by using multiple imputations. All analyses will be pre-specified in a statistical analysis plan. Statistical analyses will be performed using the statistical software IBM SPSS Statistics. SPSS will be used for descriptive statistics and all main analyses. There will be no interim analysis.

### Data collection and quality assurance

Data collection will be handled by experienced study personnel who received training in all study-related procedures, as well as good clinical practice related to the investigation of medical devices. A validated eCRF software will be used for data entry. Only authorized and trained personnel will get a password/username and are allowed to enter data. All entries and changes will be logged via an audit trail. Data management of clinical study data is handled by “Zentrum für Klinische Studien (ZKS) Kiel”. This includes eCRF construction, training and support of study sites regarding the eCRF system, query management, data cleaning and database lock. A validated study database system, Marvin (provided by XClinical), will be used. The clinical data entered into the eCRF will be stored on the XClinical servers in Nuremberg and Munich (Germany) and will be released to Frankfurt and other partners within the STIPED consortium for planned data analysis after the end of the study. Participants are informed about this procedure in the data protection paragraph of the informed consent forms. The data management plan (DMP) is issued by ZKS and describes all functions, processes and specifications for data collection, cleaning and validation. The trial monitoring will also be carried out by the ZKS, according to a pre-specified monitoring plan. Furthermore auditing procedures are specified in a separate audit plan, which encompasses auditing procedures for the whole trial as well as individual study sites regarding general quality assurance and monitoring activities, or, e.g. in case of repeated protocol-deviations.

### Documentation and evaluation of adverse events

Previous studies in children have rarely reported serious adverse events (SAEs) and tDCS-related side effects generally seem to be mostly mild and transient (such as, e.g. tingling, itching, redness and scalp discomfort [27]). In the current trial, investigators record all adverse events (AEs) in an Adverse Event Log provided in the eCRF including time of onset and intensity, causal relationship, action taken and outcome. SAEs are documented in a Serious Adverse Event Log and additionally must be reported to the sponsor immediately. The sponsor will perform all SAE-reporting to responsible authorities according to applicable national laws. A SOP on handling SAEs is provided for all trial sites by the sponsor. In Germany, quarterly safety reports listing all SAEs will be provided by the sponsor. In France and in Portugal, annual safety reports will be submitted.

A DSMB with three independent members is installed, who will monitor safety data in fixed time intervals. The first meeting will be held after the tenth patient has been included in the trial. When 50% of the participants have been recruited, the second meeting will take place. Additional meetings will be organized on demand, e.g. in case of emergency, an unscheduled meeting can be performed. If necessary, the DSMB has access to the unblinded data to judge whether the risk-benefit ratio changes throughout the study. If the board decides that the safety of participants is significantly endangered, they can recommend stopping the study.

